## Abstract

**Background:**

Antimicrobial resistance (AMR) is a rising threat in low-resource settings, largely driven by transmission in the community, outside health facilities. Inappropriate antibiotic use is one of the main modifiable drivers of AMR. Its risk is especially high in poor resource settings, with limited diagnostic and surveillance capacities, and many informal medicine vendors determining community use. We hypothesise that to optimise community antibiotic use, especially Watch antibiotics (recommended only as first-choice for more severe clinical presentations or for causative pathogens likely to be resistant to Access antibiotics), both the supply side (medicine vendors) and the demand side (communities) should be pro-actively involved in any intervention.

**Methods:**

In two existing demographic health surveillance sites (HDSS) in Burkina Faso and in the Democratic Republic of Congo, behavioural intervention bundles were co-created in a participatory approach, aiming to rationalise (Watch) antibiotic use and improve hygiene and sanitation practices. Bundles consisted of interactive interventions, including theatre, posters, discussions, etc. To evaluate impact, 11 of 22 clusters (a HDSS community with at least one (in)formal medicine vendor) were randomly assigned to this intervention, which will run over a year. The effect of the intervention will be evaluated by comparing outcomes before and after in intervention and control villages from a) exit interviews of clients from vendors, b) mystery patients presenting to vendors with a set of predefined symptoms, c) household interviews to assess behavioural changes related to antibiotic use, health literacy and water-sanitation-hygiene indicators. Long-term impact on AMR will be estimated by modelling changes in resistant Enterobacteriaceae carriage from repeated household surveys before, during and after the intervention in both arms.

**Discussion:**

Most existing interventions aimed at improving antibiotic use focus on health care use, but in resource-limited settings, community use is highly prevalent. Previous studies targeting only providers failed to show an effect on antibiotic use. Evaluation will be done with before-after epidemiological measurements of actual prescriptions and use. If effective in reducing (Watch) antibiotic use, this would be an empowering methodology for communities, which has significant promise for long-term impact.

**Trial registration:**

ClinicalTrials.govNCT05378880. 13 May 2022.

**Supplementary Information:**

The online version contains supplementary material available at 10.1186/s13063-023-07856-2.

## Background

Antimicrobial resistance (AMR) is a global health emergency, with a significant negative impact on health and socioeconomic development, in particular in low-resource settings. A major driver of AMR emergence is antibiotic use, where community-level antibiotic consumption, in addition to individual-level usage, has been associated with an increased risk of individual community members acquiring AMR bacteria [1]. As a result of difficult or delayed access to hospitals and formal health centres in many low-resource communities, self-medication with antibiotics from formal and informal medicine outlets, frequently without medically qualified staff, is widespread [2]. In sub-Saharan Africa, over two thirds of visits to community medicine stores may result in dispensing prescription-free antibiotics [3]. In the absence of a clinical or microbiological diagnosis, and with antibiotic sales a major source of revenue, community medicine outlets often dispense antibiotics without a clear rationale. Importantly, these antibiotic courses frequently consist of antibiotics classified by WHO as ‘Watch’ antibiotics, which should be restricted to specific indications due to their higher AMR potential [4, 5].

At the same time, healthcare providers or dispensers in medicine outlets may be faced with a strong demand from their communities for antibiotic treatments which, in the absence of a clinical assessment, risks to result in unnecessary or inappropriate antibiotic dispensing and usage. One RCT in India evaluated a bundle intervention targeting informal medicine outlets with an intensive multi-topic training programme over 9 months and found it improved correct clinical case management [6]. Unfortunately, a direct effect on the frequency of antibiotic use could not be demonstrated. The intervention, however, only targeted informal medicine outlets and did not seek to address the demand for antibiotics from the community.

To modify community antibiotic use and thus limit the spread of AMR, it is key to understand what factors can induce and sustain the necessary behavioural changes. At the same time, to reduce transmission of bacteria and AMR genes, as well as the burden of infectious diseases triggering antibiotic demand, strengthening of prudent WaSH practices is needed, also taking into account that in rural sub-Sahara Africa people and animals live in very close proximity. As defined by the COM-B model, behaviour is shaped by three essential conditions: capability, opportunity, and motivation, which provide intervention opportunities for behaviour change. Capabilities include psychological (e.g. knowledge) and physical (e.g. skills) capabilities. Opportunity includes social and physical opportunities (e.g. social influences and environmental context and resources). Motivation includes reflective and automatic motivation such as beliefs about capabilities and consequences, goals, and ideas about professional role and identity [7]. Target behaviours for interventions are to be based upon considerations around impact potential, likelihood for change, potential spill-over effects as well as ease of measurement.

Thus, a multifactorial approach is needed, actively involving both formal and informal healthcare providers as well as the population in the design and implementation of such stewardship interventions for a sustainable impact. This article describes the trial design by which the effect of this behavioural intervention will be evaluated on (Watch) antibiotic use, on clinical care and on water-sanitation-hygiene (WaSH) behaviour. For this, we adhered to the SPIRIT reporting guidelines [8] (Annex 1).

## Methods

### Study design

In a cluster randomised trial, we will evaluate if a year-long behavioural intervention bundle in a rural setting in Burkina Faso (Nanoro district) and in the Democratic Republic of Congo (DRC) (Kimpese district) has a superior outcome on a range of standardised AMR and WaSH indicators in intervention and control villages. Controlled measurements of antibiotic use (patient surveys), patient management (mystery patients) and water-sanitation-hygiene (household surveys) will be collected in the same season before and after. In each setting, eligible villages and town neighbourhoods (clusters) will be randomly allocated to intervention or no intervention (control). Randomisation is in two strata per site. In Nanoro, strata distinguished villages with primary health centre and those without (only formal or informal medicine outlets). In Kimpese, strata distinguished peri-urban neighbourhoods of rural villages. For each stratum, clusters (villages or neighbourhoods) are randomised 1:1 as intervention or control. A random number between 0 and 1 is given to each cluster using the RAND() function in Excel by a local data manager not involved in the trial. Half of the cluster in each of both strata, those with the higher numbers, are selected as intervention clusters; the other half, with the lower numbers, as control clusters. Allocation of villages to intervention or control was concealed until all had been recruited and baseline data available.

By randomising communities rather than individuals, contamination of intervention and no intervention should be maximally avoided, as supported by pilot studies in the DRC that observed that >80% of social contacts were with people in the same village or neighbourhood (manuscript in preparation). A steering committee consisting of the PIs of all 7 participating institutes will meet at least annually to discuss progress, and at least annually full consortium meetings will be organised with options for on-line participation.

### Study setting and population

Health demographic surveillance sites (HDSS) exist in Nanoro district, Burkina Faso, and Kimpese district, DRC where trusted long-term contacts have been built with the communities. This provides a fertile environment for high-quality studies [9]. The HDSS in Nanoro was established in 2009 and currently includes a population of about 60,000 people, living in 24 villages. 16 of these villages have a primary care health facility, to which a community pharmacy store is linked. The HDSS in Kimpese was established in 2018 and included a population of about 170,000. In the central town of each HDSS (Nanoro and Kimpese), there is a public district referral hospital, with a clinical and a research laboratory attached. Both HDSS have quality-controlled bacterial culture and antibiotic susceptibility testing capacity installed at the district hospital level. Experienced social science teams are integrated in both HDSS.

Populations in these sites are well-characterised in terms of demographics, socio-economic status, healthcare utilisation and access-to-water and hygiene parameters. Essential demographic information is updated on a continuous basis through village-based reporters, while structural information is updated during annual rounds, as well as during dedicated study visits. Baseline demographic and health indicators of households are collected at 4–6 monthly intervals, and clinical microbiology surveillance has been established in the district referral hospitals [10, 11].

Pilot studies in the HDSS of both settings, confirmed that health centres (66% in Nanoro, 68% in Kimpese), private clinics (none in Nanoro, 4% in Kimpese), community pharmacies (17% in Nanoro) and informal medicine vendors (16% in Nanoro, pharmacies and informal vendors 18% in Kimpese) were the main sources of antibiotics [12, 13]. Frequent consumption of non-prescribed antibiotics was reported by community members exiting from these local medicine stores, with a significant proportion consisting of Watch antibiotics (20% in Nanoro [14] and 24% in Kimpese [13]). Furthermore, purchased antibiotic courses were frequently underdosed or interrupted [13, 14].

Implementing the behavioural intervention bundle will not require alteration to usual care pathways and these will continue for both trial arms.

### Theoretical Framework of the Intervention

The COM-B model for behaviour change will underpin the development of the intervention [15]. Widely used in designing interventions [16], COM-B identifies three essential conditions for behaviour — capability, opportunity, motivation: Capabilities include psychological (e.g. knowledge) and physical (e.g. skills) capabilities; Opportunity includes social and physical opportunities (e.g. social influences and environmental context and resources). Motivation includes reflective and automatic motivation such as beliefs about capabilities and consequences, goals, and ideas about professional role and identity [7].

### Intervention development and implementation

Each intervention cluster will be visited 3 times over the period of a year, for one week at a time. The intervention bundle targets behaviours which are shaped by identified drivers of AMR. These drivers either affect the selective pressure by antibiotics on bacteria, or the transmission of AMR bacteria. At the community level in low-income settings such as Nanoro or Kimpese, drivers of AMR include suboptimal health literacy of the population, suboptimal selling practices of antibiotics in medicine stores, limited timely access to formal healthcare, poor formal healthcare provisioning of diagnostic tools and services, and widespread incidence of infections related to poor hygiene and sanitation (Fig. 1).

**Fig. 1 Fig1:**
[figure not shown]
Drivers of AMR, guiding the development of the behavioural intervention

Intervention development during the initial 8 months of the project followed the gold standard Intervention Mapping framework, with 6 crucial steps for intervention development [17, 18]. A preparatory phase, utilising Photovoice methodology [19], focus group discussions and individual interviews, explored determinants of antibiotic misuse and drivers and barriers to change. Analysis of the data gathered during the preparatory stage resulted in the participatory co-creation of the intervention bundles (for example, many communities suggested theatre as an effective form of generating discussion), as well as the most appropriate angles for discussion: for example, targeting local vendors in DRC using the idea of their vital signposting role, and emphasising their importance in safeguarding the health of the community.

A detailed context-specific day-to-day description of activities with the communities (adults, adolescents, schools) and with the formal and informal providers was subsequently developed for each HDSS.

The first component of the intervention bundle targets medicine stores, incorporating a series of individual and group sessions with both formally trained community pharmacy staff as well as informal vendors of antibiotics focusing on when antibiotics should and should not be used, as well as communication skills with customers.

The second component of the intervention bundle targets the general population and intends to increase community health literacy around health care use and communication with health care providers. Health literacy is a key concept in reducing incorrect antibiotic use, entailing “knowledge, motivation and competences to access, understand, appraise, and apply health information in order to make judgements and take decisions in everyday life concerning healthcare, disease prevention and health promotion to maintain or improve quality of life during the life course.” [20].

The third component of the intervention bundle targets the general population, focusing on improving water and hygiene and sanitation practices in order to prevent infectious illness and the (perceived) need for antibiotics. Activities determined upon by the teams include discussions with village and religious leaders, theatre and films, school games, and ad-hoc sessions. The activities used for these components draw on the ideas around hygiene and disgust [21, 22], activities from the World Bank’s Handwashing Handbook and successful WASH interventions such as SuperAmma [23]: the ADAPT guidelines were followed in the adaptation of certain activities from SuperAmma [24].

There will be no special criteria for discontinuing or modifying allocated interventions.

### Timeline

The timeline is shown in Fig. 2.

**Fig. 2 Fig2:**
[figure not shown]
Timeline. (Legend: DRC, Democratic Republic of Congo; BF, Burkina Faso)

### Objectives

#### Primary objectives

Develop, implement, and evaluate the effect of a behavioural intervention bundle targeting medicine stores (including community pharmacies and informal medicine sellers), and the surrounding populations on (Watch) antibiotic use.Develop and pilot environmental AMR surveillance through rodent surveillance.Estimate and model the effect of the intervention bundle on AMR prevalence and transmission, focusing on faecal E. coli and Salmonella carriage.

#### Secondary objectives

Estimate the intervention bundle’s effect on hygiene, on case management by medicine stores and on clinical outcomes.Identify pathways and incentives through which educational or peer influence interventions improve quality of care.Compare prevalence of AMR bacterial populations in human (i.e. household members) and rodent reservoirs; compare with AMR prevalence in routine BSI surveillance.Spatial and ecological analysis as well as phylogenetic comparison of AMR bacterial populations and genetic clones identified in human carriers and dwelling rodents.Quantify household transmission of AMR genes or pathogens and estimate the relative importance of an environmental transmission source.

### Outcomes

#### Primary outcome

Changes in use of (Watch) antibiotics from health centres and medicine stores.Estimated changes in AMR community carriage.

#### Secondary outcomes

Assessment of impact of educational or peer influence interventions on improved antibiotic use, quality of care, health literacy and WaSH practices.Estimate households’ risk of community-level AMR transmission, including WaSH conditions and behaviour, contact with domestic animals.Changes in correct patient management, estimated from simulated patient visits, during which so-called mystery patients present with well-defined and common infectious disease-related clinical presentations.

### Eligibility

All villages or neighbourhoods with at least one health centre or medicine outlet and at least 500 inhabitants are eligible to be recruited as study cluster. If more such villages are present, the villages with the larger number of medicine outlets will be selected. Medicine outlets take different forms, going from community pharmacies with medicine dispensed by staff with various qualifications, to medicine shops owned by qualified healthcare workers but with actual medicines dispensed by lay staff, to fully informal medicine vending in regular shops or on markets. All community members or providers present at the time of assessments or interventions were invited to participate. The unit of randomisation corresponds to a village with at least one medicine store.

### Sample size

The sample size is based on the primary outcome. Including in each setting 22 clusters, with per cluster 100 patients to be interviewed upon exiting a medicine store, a frequency of Watch antibiotic use of 24% in DRC [13], and assuming an estimated intraclass coefficient of 0.05, a cluster level correlation (rho_c_) of 0 (conservative), subject level correlation (rho_s_) of 0 (different subjects at baseline and at 12 months), our study has 80% power to observe a 40% reduction in Watch antibiotic use.

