
### Analysis

The effect evaluation will use standard experimental methods and will make use of multilevel statistical models (to account for clustering within villages and households), including time*intervention interactions. The population’s socio-demographics, socio-economic status, healthcare use and health behaviour are regularly recorded during scheduled HDSS rounds, which will allow subgroup analyses of the effect of the intervention.

Based on the exit interviews, the proportion of primary care or medicine outlet visits resulting in dispensing of Watch antibiotic courses will be estimated, adjusted for clustering, in the intervention and in the control groups before and 12 months after the start of the intervention. Antibiotics will be grouped as Access, Watch or Reserve (AWaRe) according to WHO’s 2019 AWaRe classification. Patients’ antibiotic treatment dose, dosage, duration, mode of administration and uptake will be assessed, to determine the Defined Daily Doses (DDD) each treatment course accounts for. We assess for each treatment course whether the treatment is underdosed, based on the 2022 WHO AWaRe Antibiotic Book. A case management score is deducted using the scoring grid to be completed after each simulated patient visit. The change in frequency of Watch antibiotic use and in mean case management score before and after the intervention (months 0 and 12) will be compared to that during the same period in the control areas. We will determine risk differences and risk ratios, which will be adjusted for socio-economic indicators and other potential confounding factors. Linear and non-linear regression models will be used to estimate the effect and carry out subgroup analyses.

Stool samples will be cultured on selective CHROMagar™ plates and species identified. If *E. coli* and/or *Salmonella* isolates are detected, they will be typed and antibiotic susceptibility testing done according to CLSI guidelines for pathogen-antibiotic indicators and for ESBL, if the minimal inhibitory concentration for ceftriaxone or ceftazidime is above 1 mg/L.

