### Trial status

Following external peer review, the study protocol was selected by JPI for funding on 28 October 2021 (JPIAMR2021-053) with a total budget of 1.6 million Euro, and registered at www.clinicaltrials,gov on 13 May 2022 (NCT05378880). In 2022, the development of the intervention bundles and materials took place through a co-creation process with the communities, per country 22 clusters were identified, and pre-trial data collection started in both arms. Implementation of intervention bundles started in February 2023 and is ongoing, with post-intervention bundle data collection in both intervention and control villages expected to be completed by summer 2024 (Figs. 3 and 4).

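### The stated 80% power is not tied to one country or to both, and on the protocol's own inputs it fits neither

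*Protocol article*

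**What the plan says.** The Sample size section sets out "Including in each setting 22 clusters, with per cluster 100 patients to be interviewed upon exiting a medicine store". It assumes "a frequency of Watch antibiotic use of 24% in DRC", an intraclass coefficient of 0.05, and cluster-level and subject-level correlations of 0. From these it claims 80% power for a 40% reduction in Watch use, and attributes that power to the study without saying whether one setting or both are meant.

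Elsewhere in the protocol article:

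- Trial status: "per country 22 clusters were identified", so 44 in total.
- Abstract, Methods: "11 of 22 clusters (a HDSS community with at least one (in)formal medicine vendor) were randomly assigned to this intervention", without saying whether this is per country.
- Study design: one cluster randomised trial with two strata per site. "For each stratum, clusters (villages or neighbourhoods) are randomised 1:1 as intervention or control".
- Analysis: the proportion of visits ending in a Watch course "will be estimated, adjusted for clustering, in the intervention and in the control groups before and 12 months after the start of the intervention". Multilevel models with a time-by-intervention interaction are planned, and the change in intervention areas is compared with the change in control areas. No country level is mentioned.
- Study setting and population: the pilot share of Watch antibiotics was 20% in Nanoro and 24% in Kimpese. Only the second enters the sizing.

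Neither alpha nor sidedness is stated.

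**The concern.** A power figure has meaning only for a named comparison. Here the cluster count is given per setting, the event rate comes from one setting, and the power is given for the study. A reader cannot tell whether 80% describes a 22-cluster comparison, made once or twice, or a 44-cluster comparison.

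If the figure is per country, each country is considerably less well powered than stated. If it is for the pooled trial, the answer depends on whether follow-up values or before-after changes are compared. Because the unit is open, the same results could be declared negative in each country or positive overall, and nothing in the article fixes that choice before the data are seen.

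**Working it through.** **Inputs.** From Sample size: control proportion p1 = 0.24, 40% reduction, ICC = 0.05, m = 100 per cluster, both correlations 0, 22 clusters per setting. From Study design: 1:1 allocation, so 11 per arm per country and 22 per arm pooled. From Study setting and population: 0.20 for Nanoro. Assumed: two-sided 5%, and the 40% read as relative, so p2 = 0.6 × 0.24 = 0.144 (an absolute fall of 40 points from 24% is impossible).

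**Effective sample size.** Design effect = 1 + (100 − 1) × 0.05 = 5.95. One country: 1,100 / 5.95 = 184.9 per arm. Pooled: 2,200 / 5.95 = 369.7 per arm.

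**Attempt to reproduce 80% with the follow-up contrast.** With both correlations at 0, baseline adjustment gains nothing, so this also covers a baseline-adjusted analysis.

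- SE = √[(p1(1 − p1) + p2(1 − p2)) / n_eff], with 0.1824 + 0.1233 = 0.3057 in the numerator.
- One country: SE = 0.0407; 0.096 / 0.0407 = 2.36; power = Φ(2.36 − 1.96) = 65.6%.
- Pooled: SE = 0.0288; ratio 3.34; power = Φ(1.38) = 91.6%.
- With a t reference distribution on the clusters: 61.3% and about 90%.

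**Before-after change contrast (Analysis section).** With zero correlation between rounds, the variances of four arm-by-round proportions add, three at 24% and one at 14.4%: 3 × 0.1824 + 0.1233 = 0.6705.

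- One country: SE = 0.0602; ratio 1.59; power = 35.7%.
- Pooled: SE = 0.0426; ratio 2.25; power = 61.6%.

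**Summary**

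| Baseline rate | Clusters per arm | Follow-up | Change |
|---|---|---|---|
| 24% | 11 (one country) | 65.6% | 35.7% |
| 24% | 22 (pooled) | 91.6% | 61.6% |
| 20% (to 12%) | 11 (Nanoro) | 56.0% | 29.5% |

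If the DRC is at 24% and Nanoro at 20%, each with a 40% reduction, the pooled stratified follow-up contrast has about 89%.

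**What would give 80%?** The two-proportion formula needs 264 per arm before clustering: 264 × 5.95 / 100 = 15.7 clusters per arm, between 11 and 22. A one-sided 5% test in one country gives 75.9%. The nearest match is 44 clusters with the 40% read as an odds ratio of 0.6 (24% to 15.9%), at 78.5%, but the text does not say this. Otherwise the ICC would have to be about 0.032 (one country) or 0.074 (pooled) instead of 0.05.

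**Can the choice change the conclusion?** Suppose 24% versus 17% is observed at follow-up in both countries. Then 0.1824 + 0.1411 = 0.3235.

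- Each country: SE = √(0.3235 / 184.9) = 0.0418; z = 0.07 / 0.0418 = 1.67; p = 0.094.
- Pooled: z = 1.67 × √2 = 2.37; p = 0.018.

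On the change contrast, with 24% in the other three cells, the same happens at an observed 14%: SE = √[(3 × 0.1824 + 0.1204) / 184.9] = 0.0601; z = 1.66 and p = 0.096 in each country; z = 2.35 and p = 0.019 pooled.

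**The case against.** Whether two sites are pooled, and which country terms enter the model, is ordinary analysis-plan content. The article is condensed and no analysis plan is shown. The passages can be reconciled: sizing, allocation and cluster identification are all described per setting, and the abstract's "11 of 22 clusters" reads easily as a per-country count. Separate country estimates are also defensible. The activities were developed for each site, and the Limitations section says that the intervention is context-specific and not generalisable by design. Pooling is therefore partly a preference.

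Most of this stands. Silence on pooling is not in itself an error, and the cluster counts do not contradict each other. It does not rescue the power statement: the comparison behind a published power figure belongs with that figure, and the per-setting reading, which is the most natural one, gives 66% at best under a two-sided 5% test.

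A reader might go further and infer that two country tests give this trial a 9.75% false-positive risk (1 − 0.95² = 0.0975). The document does not support that. It requires 5% per test and a rule that success in either country makes the trial positive, and neither is stated. If both countries had to succeed, the risk would be 0.05² = 0.25%. If only benefit counted under two-sided 5% tests, it would be 1 − 0.975² = 4.94%. If each country is its own question, each test keeps its own alpha.

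A reader might also infer that one significant and one non-significant country is the likeliest outcome of separate tests. That depends on per-country power. At 65.6% follow-up power, exactly one is significant with probability 2 × 0.656 × 0.344 = 45%, against 43% for both. At a true 80% it would be 32% against 64%. It is a consequence of the power shortfall and not a separate defect.

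**Conclusion.** The point holds as a defect in the sample-size statement. Its unit, country or whole trial, is not identifiable, and the 80% is reproduced for neither unit on either contrast: 66% and 92% at follow-up, 36% and 62% for change. The Nanoro rate lowers the single-country figures to 56% and 30%. The unit matters in practice, since plausible results can fall on opposite sides of 5% depending on it.

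The figures assume a two-sided 5% test, a relative reduction, equal cluster sizes and the stated zero correlations. A positive cluster-level correlation would raise power for the change contrast, but the protocol sets it at 0. The point does not establish an inflated error rate, nor that a pooled test must be primary.

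**What to change.** In Sample size and Analysis, name the comparison that decides Watch use, including whether it is a follow-up or a change contrast. State alpha and sidedness, and restate the power or the detectable reduction for that comparison. For a follow-up contrast at a 24% rate, 80% power corresponds to a reduction of about 47% with 22 clusters and about 34% with 44.

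- **Option 1, pooled.** Estimate one intervention effect over all 44 clusters, with country and the randomisation strata as fixed effects. Give country-specific effects and the country-by-intervention interaction as secondary results. The drawback is a headline averaged over two context-specific bundles.
- **Option 2, per country.** State that each country is its own question, or set a multiplicity rule (for example 2.5% each if either could carry the claim). Restate power for each country with its own pilot rate.

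In the abstract, say that 11 of 22 clusters is per country. All of this is wording and a recalculation, with no extra clusters, patients or data collection. Under Option 2 the cost is acknowledging lower power or a larger detectable effect.
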